### 2.1. Eligibility Criteria

Eligible care recipients will be aged 65 years or older, English or Spanish-speaking, community-dwelling, and have no contraindications to engaging in physical activity. They must be willing to wear a smartwatch, receive text messages, watch intervention-related videos, and participate in video-guided physical rehabilitation sessions and walking exercises. Care recipients will be ineligible if they do not have a care partner or have severe cardiac, neurologic, or musculoskeletal conditions (including, but not limited to, a recent joint replacement or recent or untreated fractures in any part of the body) that limit participation in walking exercise or smartwatch use. Also, they will be excluded if they have moderate to severe dementia and are unable to operate or manage a smartwatch even with care partner support. Additionally, they will be excluded if they have no internet, phone, or any devices capable of receiving text messages or watching educational or physical therapy-related videos.

Similarly, eligible care partners must be at least 18 years old. They must be the legally authorized representative of the care recipient when the care recipient lacks the capacity to consent. They must live with or within five miles of the care recipient and be able to co-participate in all aspects of the ACTIVE intervention. They will be ineligible if they have severe cardiac, neurologic, or musculoskeletal conditions (including but not limited to recent or untreated fractures in any part of the body), limiting participation in walking exercise or smartwatch use. Also, they will be excluded if they have moderate to severe dementia, are unable to operate or manage a Fitbit smartwatch, have no internet, phone, or any device capable of receiving text messages or watching educational or physical therapy-related videos.

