### 2.3. Randomization

Participants will be assigned to study arms after completion of the baseline enrollment survey. The study staff who enrolls each participant will notify the study biostatistician, who will provide the allocation. Randomization will be conducted using a computer-generated, permuted block randomization sequence stratified by dyad type (with or without mild AD/ADRD). Within each stratum, randomization will be performed using permuted blocks of 4 to ensure balanced group sizes. Both members of the dyad will be randomized together to the same intervention or control arm. The randomization sequence will be generated in advance by the study biostatistician using a random number generator and securely maintained within the study database, accessible only after baseline data collection is completed. After the third week of intervention, we will have a one-week crossover period, and all participants will switch to the alternate study arm. This one-week crossover period is a washout period to minimize the effects of promptings and motivations produced by the text messages, rather than to eliminate retained knowledge or behavior change. Group assignments will remain linked to each participant’s unique study ID throughout the study. The analyst will remain blinded to group assignments until data cleaning, feasibility, and preliminary efficacy analyses are complete.

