### 2.5. Intervention Design

The ACTIVE intervention consists of six co-occurring events as follows (Table 1):

Activity Tracking: Care recipients and their care partners will be provided with a wrist-worn Fitbit smartwatch to wear during waking hours for at least 8 h per day. Activity metrics will be tracked for care recipients and care partners on Fitabase.

Care partner co-participation: Care partners will play active, structured roles in the intervention. These roles include (1.) Safety oversight, (2.) Co-engagement, (3.) Education access and (4.) Motivation and supervision. Care partners will be required to ensure their care recipients use the smartwatch consistently, walk safely, and adhere to exercise protocols (safety oversight). They will participate in walking exercises and video-guided physical rehabilitation sessions together with their care recipient (co-participation). They will view educational videos to understand how best to support care recipients to stay active in safe environments (education). Lastly, they will encourage adherence, monitor fatigue, and help adjust routines as independence improves (motivation and supervision). Care partner engagement will be assessed using a multimodal approach, including platform-based analytics (login frequency, module completion), structured prompts embedded within myACTIVEsteps, and brief scheduled daily text message check-ins to capture real-time participation and support activities.

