### 2.8. Sample Size Determination

For this pilot study, the trial is not powered to detect clinical efficacy but to provide adequate precision for estimating feasibility metrics and to inform the design of a future fully powered effectiveness–implementation trial [44]. We will enroll 50 dyads (older adult + care partner), a recommended sample size for behavioral pilot trials and digitally delivered rehabilitation interventions [44,45,46]. A sample of 50 dyads (n = 100) provides adequate precision to estimate key feasibility parameters that guide go/no-go decisions.

For a feasibility outcome, the unadjusted standard error (SE), assuming independence, is estimated using the formula in Equation (1). Using an expected proportion of 0.75 (e.g., completion of ≥75% of virtual PT modules), the unadjusted SE is 0.043.(1)SE=p (1−p)n

To account for dyadic clustering, we assume an intra-cluster correlation (ICC) of 0.1–0.3, which is typical for partner dyads [47,48]. Using the design effect formula in Equation (2), an ICC of 0.2, and a cluster size (m) of 2, the design effect is 1.2, and the cluster-adjusted SE (Equation (3)) is 0.047. The cluster-adjusted 95% CI for a 75% completion rate (Equation (4)) is therefore 0.66–0.84.Design Effect = 1 + (m − 1) × ICC(2)Cluster-adjusted Standard Error (adjusted SE) = Unadjusted SE × √(Design Effect)(3)(4)95% CI=p±1.96×adjusted SE

This level of precision is appropriate for feasibility-focused pilot research, where the goal is to estimate plausible ranges and plan thresholds for an adequately powered future trial.

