### 2.13. Analysis Plan

Handling of Missing Data: We anticipate low levels of missing data, which will be assessed for randomness using Little’s test [63,64]. Multiple imputation with chained equations will be used when appropriate [65,66,67], with sensitivity analyses to evaluate robustness of results. For feasibility outcomes, missing data will be minimized through proactive monitoring and participant reminders, and patterns will be summarized descriptively. For preliminary efficacy analyses, linear mixed-effects models will accommodate incomplete longitudinal data under an intention-to-treat framework. The percent and potential impact of missing data will be reported.

Feasibility Assessment: Six feasibility outcomes (recruitment, adoption, adherence, acceptability, fidelity, retention): will be summarized overall and stratified by AD/ADRD status (dyads with mild AD/ADRD and dyads without mild AD/ADRD) and by participant role within the dyad (care recipient vs. care partner). We will report the proportions and mean distributions, including 95% confidence intervals, for the feasibility measures, and descriptively compare these values with the preset benchmark (Table 3). A “go” decision will be made if the majority of benchmarks are met, a “conditional go” if some but not all benchmarks are achieved (with justification for modifications), and a “stop” decision if most benchmarks are not met. Feasibility outcomes will be assessed separately by AD/ADRD status and by intervention and control arms. Differences in feasibility outcomes by AD/ADRD status and by participant role will be explored descriptively using mean differences and differences in proportions with 95% confidence intervals.

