Preliminary Efficacy Assessment: Using linear mixed-effects models, we will estimate the effect size of the ACTIVE intervention’s preliminary efficacy on the three activity metrics and seven post-intervention behavioral measures (listed above). The effect size will be estimated from the pre-crossover phase (Equation (5)). Full six-week mixed-effects models are used to evaluate whether longitudinal patterns remain consistent with the pre-crossover estimate, after accounting for the impact of the crossover and the sequence of intervention (Equation (6)). The random intercept will account for both within-dyad correlation and repeated measures. Fixed effects will include treatment (intervention vs. control), sequence (intervention first or last), baseline values of the outcomes, dementia status (mild AD/ADRD vs. no AD/ADRD), treatment × dementia interaction, period (pre-crossover vs. post-crossover), treatment × period interaction, and covariates to assess potential differential effects. For participant *i* in dyad *d* at time *t* (t = baseline, follow-ups), the outcome will follow the mixed effect model in Equations (1) and (2), as follows:(5)$${\;Y}_{idt}=\;\beta_{0}+\;\beta_{1}{Trt}_{i}+\;\beta_{3}{Time}_{t}+\;\beta_{5}Y_{id0}+\;\beta_{6}{Dem}_{i}+\;\beta_{7}\left({Trt}_{i}\;\times \;{Dem}_{i}\right)+\;\tau^{T}X_{i}+\;b_{d}+\;b_{i\left(d\right)}+\;\in_{idt}\;\;$$(6)$$Y_{idt}=\beta_{0}+\beta_{1}{Trt}_{i}+\beta_{2}{Seq}_{i}+\beta_{3}{Time}_{t}+\beta_{4}{Period}_{t}+\beta_{5}Y_{id0}+\beta_{6}{Dem}_{i}+\beta_{7}\left({Trt}_{i}\times {Dem}_{i}\right)+\beta_{8}\left({Trt}_{i}\times {Period}_{i}\right)+\tau^{T}X_{i}+b_{d}+b_{i(d)}+\in_{id\;\;\;\;\;\;\;\;}$$

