where *Y_idt_* = outcome, *β*_0_ = fixed intercept, *Trt_i_* = treatment indicator, *Seq_i_* = sequence indicator, *Y_id_*_0_ = baseline value of the outcome, *Demi* = dementia status, *Trt × Dem* = treatment-by-dementia interaction, *Trt × Period =* treatment-by-crossover interaction, γ^⊤^*X_i_* = coefficient of covariates, and *b_d_* and *b_i(d)_* are the random intercept for dyad and individual nested within dyad, respectively. Treatment condition (intervention vs. control) and sequence (intervention-first vs. intervention-second) will be included as fixed effects to estimate the average intervention effect and to account for between-participant differences related to assignment order, respectively. Time will be modeled as a continuous weekly measure to capture trends over the six-week follow-up. Period will be modeled separately as a categorical indicator of pre- versus post-crossover phase to distinguish underlying activity trajectories from changes associated with withdrawal of active intervention components. Given the anticipated persistence of learning effects due to the short one-week washout period, the treatment × period interaction will be used to characterize maintenance or attenuation of intervention effects rather than to assume their absence. All analytical models will follow the intention-to-treat principle, and effect sizes with 95% confidence intervals will be reported to inform power calculations for a future definitive trial.

Qualitative Assessment: Semi-structured interviews will be conducted with dyads after completing the intervention phases. Dyads initially randomized to the intervention arm will be interviewed at crossover, while those starting in the control arm will be interviewed after completing the delayed intervention. Interviews will explore barriers and facilitators to smartwatch use, motivational texts, instructional educational modules, engaging in video-guided physical rehabilitation, walking exercise, and co-participating with a care partner. While we estimate conducting 10 to 20 interviews each for those with and without mild AD/ADRD, the exact number will be guided by the achievement of thematic saturation [68,69].

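### Equations 5 and 6 pool care recipients and care partners with no role or treatment-by-role term, so no effect in older adults can be read from the model

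*Protocol article*

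**What the plan says.** All references are to the protocol article.

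- **Who is in the trial (2.1, 2.3).** "Eligible care recipients will be aged 65 years or older", whereas "eligible care partners must be at least 18 years old". On allocation: "Both members of the dyad will be randomized together to the same intervention or control arm".
- **Who supplies outcomes (2.5, 2.12).** "Activity metrics will be tracked for care recipients and care partners on Fitabase". Section 2.12 has both members repeat the baseline surveys.
- **The models (2.13).** Equations 5 and 6 are written for a participant within a dyad. They carry two random terms that "are the random intercept for dyad and individual nested within dyad, respectively". The listed fixed effects are treatment, sequence, baseline value, dementia status and treatment × dementia, then period, and they end with "treatment × period interaction, and covariates to assess potential differential effects". The covariates in 2.11 are sociodemographic items, frailty and comorbidity. Role appears in none of these places.
- **Where role does appear (2.13).** The feasibility outcomes are summarised "by participant role within the dyad (care recipient vs. care partner"). The efficacy paragraph has no such split.
- **What the estimates are for (2.13).** Effect sizes with 95% CIs are to feed the power calculation of a later definitive trial.

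**The concern.** Intercepts for individuals nested within dyads make sense only if both members enter the same model. With no treatment × role term, that model assumes the intervention does the same for a recipient and for a partner.

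The design gives reason to doubt this. The two roles have different age limits (2.1). Their educational videos differ: moving, exercise and fall prevention for recipients; supervision, safe environments and risk recognition for partners (2.4). Partners also have oversight and supervision tasks (2.5). The authors treat role as meaningful for feasibility in the same section.

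At stake is a main product of the pilot. The abstract sets the goal as more physical activity among older adults, but neither equation yields an effect size for them. A definitive trial aimed at older adults would be planned on a mixture of two effects in unknown proportion to the one it needs. Age and baseline value in the model can absorb part of a difference in level between roles, but not a difference in treatment effect.

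**Working it through.** **1. The plan's own figures (2.8).** On size, the plan says: "A sample of 50 dyads (n = 100) provides adequate precision to estimate key feasibility parameters". With p = 0.75 and n = 100, SE = √(0.75 × 0.25 / 100) = 0.0433. Design effect = 1 + (2 − 1) × 0.2 = 1.2. Adjusted SE = 0.0433 × √1.2 = 0.0474. The 95% CI is 0.75 ± 1.96 × 0.0474 = 0.657 to 0.843. The stated 0.043, 1.2, 0.047 and 0.66–0.84 reproduce and are not in dispute. The plan gives no efficacy effect size or SD, so the effects below are assumptions, in SD units.

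**2. What the coefficient estimates with equal weights.** There is one recipient and one partner per dyad, always in the same arm. Averaged over dementia strata, pooled effect = (recipient effect + partner effect) / 2. The n per arm uses 2 × (1.96 + 0.8416)² / effect² (two-sided 5%, 80% power). The recipient effect is set at 0.50, which alone would need 63 per arm.

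| Assumed partner effect | Pooled effect | n per arm from pooled effect |
|---|---|---|
| 0 | 0.25 | 252 |
| 0.25 | 0.375 | 112 |
| 0.50 | 0.50 | 63 |
| 0.75 | 0.625 | 41 |

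The error can go either way. In the last row, 41 per arm gives about 62% power for a true recipient effect of 0.50.

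**3. Simulation check.** Data were simulated for 50 dyads with three weekly measures, dyad and individual intercepts, baseline value and treatment × dementia (dementia per dyad and centred), with 100 replicates per row. The model without role gave mean treatment effects of 0.257, 0.381, 0.496 and 0.629. Adding role and treatment × role gave mean recipient effects of 0.494, 0.508, 0.496 and 0.503.

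**4. Why equal weights are only an illustration.** Under 0/1 coding with treatment × dementia fitted, the coefficient β1 is the effect where Dem = 0.

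- If Dem is a dyad attribute, that group is the 25 dyads without AD/ADRD: 25 recipients and 25 partners, so equal weights within it.
- If Dem is a participant attribute, as its subscript suggests, and no partner has dementia (assumed), Dem = 0 holds 25 recipients and 50 partners, and Dem = 1 holds 25 recipients. Ignoring within-dyad correlation, β1 = (25 × 0.50 + 50 × partner effect) / 75. That is 0.167 for a partner effect of 0 and 0.667 for 0.75. The apparent treatment × dementia term would be 0.50 − 0.167 = 0.333 or 0.50 − 0.667 = −0.167, even with identical effects in recipients with and without dementia. It would be a role contrast under another label.

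**5. Price of separating the roles.** These are 95% half-widths for a simple between-arm comparison, before baseline adjustment and ignoring repeated measures and the dementia interaction.

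- Recipients only, 25 per arm: 1.96 × √(2/25) = 0.55 SD.
- Pooled, 50 individuals per arm, ICC 0.2: 1.96 × √(2 × 1.2/50) = 0.43 SD (0.41 to 0.45 for ICC 0.1 to 0.3).
- Difference between role effects, ICC 0.2: 1.96 × √(2 × (1 − 0.2) × 2/25) = 0.70 SD.

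**The case against.** The strongest reply is that a dyad average is what the authors want. The second aim in the Introduction is framed around the dyads, and 2.13 describes the target as an average intervention effect. That stands: the dyad average is a legitimate quantity. It does not remove the gap, because a model with treatment × role still delivers the dyad average as the mean of two role effects, whereas the printed model cannot deliver the recipient effect.

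A reader might go further and infer that the older-adult effect is diluted, or that the definitive trial would come out four times too large (252 against 63). The documents do not support either.

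- They give no role-specific effects. Partners join the walks and rehabilitation sessions and receive texts tailored to their own activity, so a smaller partner gain in steps or METs is not evident.
- Dilution is most plausible for fall risk, fear of falling and ADL/IADL, where independent partners may have little room to change. But 2.7 and 2.12 describe mid-study surveys for the intervention arm only. Without control-arm surveys before crossover, Equation 5 lacks a between-arm comparison for those outcomes, with or without role.
- The fourfold ratio needs a partner effect of zero, equal weights and a later trial that analyses recipients only. If that trial also analysed both members at ICC 0.2, the ratio in dyads would be 4 × 1.2 / 2 = 2.4.

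Two further points carry some weight. Section 2.8 says the trial is not powered for efficacy, and the Discussion concedes that dyadic interdependence cannot be fully isolated at this size. Both argue for modest claims about role differences. Neither explains leaving role out of models that are printed in full and already include dementia and period as effect modifiers. For that reason this is also not merely detail left to an unseen analysis plan.

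**Conclusion.** The point holds as a gap in the specification, not as a bias of known direction. Both equations pool the two roles, and the treatment coefficient is a role-averaged effect within the dementia reference group. It equals the recipient effect only if both roles respond alike, falls below it if partners gain less, and exceeds it if they gain more. With an assumed recipient effect of 0.50 SD and equal weights, the coefficient lies between 0.25 and 0.625 SD for partner effects between 0 and 0.75 SD. These are illustrations, since the documents supply no effect by role. The level at which Dem is coded is also unsettled and changes the weights. What rests on the text alone is that no care-recipient effect can be read from the model as written, although its estimates are intended for planning the definitive trial.

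**What to change.** Add Role and Trt × Role to Equations 5 and 6, keeping the dyad and individual intercepts. State whether Dem is a dyad-level or a participant-level variable. For each outcome, report the care-recipient and care-partner effects with 95% CIs beside the dyad average. Use the care-recipient estimate when planning a trial aimed at older adults.

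The cost is analysis wording and two more coefficients per model, with no new data for the Fitbit activity metrics. The recipient interval is wider than the pooled one, as calculated above. The role difference itself is estimated too imprecisely (about ±0.70 SD) for a test of it to decide whether to pool, so both role effects should be reported whatever that test shows.

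The change serves the activity metrics directly. For the survey outcomes it helps only if control-arm surveys before crossover are available, so the authors should confirm whether they are collected.

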### 2.14. Ethical and Safety Considerations

This study was approved by the NYU Langone Health Institutional Review Board (IRB# i25-01158; 22 December 2025) and is registered on ClinicalTrials.gov (NCT07321587; Registration Date: 23 December 2025) [78]. All participants will provide electronic informed consent prior to participation. We will conduct the study in accordance with all applicable ethical guidelines for human subject research and comply with institutional and federal guidelines. To protect participant safety and confidentiality, all research personnel have completed comprehensive training in human subject protection. All data will be stored securely, de-identified when appropriate, and accessed only by authorized study staff. Any substantive protocol amendments will be reviewed and approved by the IRB, updated on ClinicalTrials.gov as applicable, and communicated to study participants when relevant. This protocol follows the Standard Protocol Items: Recommendations for Interventional Trials (SPIRIT) guidelines [79].

Given the minimal-risk, behavioral nature of the ACTIVE intervention, no formal Data Monitoring Committee is required. Interim analyses will be conducted intermittently for participant monitoring. Trial conduct, data quality, and participant safety will be monitored on an ongoing basis by the study principal investigator and designated study staff in accordance with IRB-approved procedures. Any unanticipated problems or adverse events will be reported promptly to the IRB in accordance with institutional policies.

The study team will continuously assess the potential benefits and harm associated with the study. The potential benefits include improved physical activity engagement, reduced fall risk, and enhanced quality of life among older adult–care partner dyads with and without mild AD/ADRD. Potential harms, including physical, psychological, and technical adverse events, will be systematically monitored throughout the study. Feasibility outcomes will help identify unintended challenges or barriers, ensuring a careful assessment of the intervention’s positive and negative impacts.

## 3. Discussion

This pilot study is designed to evaluate the feasibility and preliminary efficacy of the ACTIVE intervention, a novel, theory-guided, multi-component, dyadic digital health intervention targeting physical activity engagement, fall risk, and quality of life among community-dwelling older adults with and without mild AD/ADRD and their care partners. The study addresses a critical gap in fall prevention and physical activity promotion research by integrating wearable technology, video-guided physical rehabilitation, educational content, motivational messaging, and structured care partner involvement into a single, scalable intervention delivered entirely in the home setting.

The expected findings will contribute to the growing body of evidence supporting digitally delivered, community-based physical activity interventions for older adults, particularly those at elevated risk for falls and functional decline [80,81,82,83]. Feasibility outcomes will be particularly informative for future trial design. Demonstrating adequate recruitment, retention, and adherence among dyads, including those with mild AD/ADRD, would provide strong justification for inclusion of this high-risk population in larger digital health trials. Similarly, detailed engagement metrics captured through myACTIVEsteps.com and Fitabase will allow identification of which intervention components are most strongly associated with sustained participation, informing optimization and potential streamlining of the intervention for broader dissemination. Although this pilot is not powered to detect definitive clinical effects, preliminary efficacy estimates will provide critical signals regarding the potential impact of ACTIVE on objective physical activity metrics, fall-related outcomes, functional independence, and quality of life. Improvements in physical activity behaviors, even over a short intervention period, may support the plausibility of longer-term benefits, aligning with prior studies demonstrating sustained effects of physical activity and digital health interventions among older adults with longer follow-up [81,84,85]. The qualitative component of this study will further contextualize quantitative findings by elucidating barriers and facilitators to engagement with each intervention component. Insights from care recipients and care partners will inform refinements related to messaging frequency, technological burden, cognitive accessibility, and the balance between independence and supervision. The result of this pilot study will directly inform the design of a future definitive effectiveness–implementation hybrid trial.

This pilot study has its limitations. The small sample size and short intervention period limit our ability to draw definitive conclusions about efficacy or long-term outcomes, but are appropriate for establishing feasibility, acceptability, and preliminary effect sizes to inform sample size calculations for a larger trial. Recruitment through ResearchMatch may enrich the sample with individuals who are more technologically comfortable or health-motivated, reducing generalizability to the broader population of community-dwelling older adults. Older adults with mild AD/ADRD may face unique cognitive and attentional challenges that could affect comprehension of instructions, consistent device use, and accuracy of self-reported outcomes. At the same time, care partners’ engagement may vary substantially based on competing responsibilities and caregiver burden. While the requirement for a co-residing or nearby care partner was included to ensure adequate exposure to intervention and safety monitoring, it may limit generalizability. The study relies on self-reported survey measures, which may introduce recall and social desirability bias, as well as discrepancies between perceived and actual behavior [86,87]. To mitigate recall and social desirability bias among participants with mild AD/ADRD, we will employ several strategies. Care partners will be permitted to assist with recall when needed, though we acknowledge this may introduce proxy reporting considerations. To address social desirability bias, we will emphasize the confidentiality of responses and use neutral, non-judgmental language during data collection. Where possible, self-reported measures will be triangulated with objective data captured on Fitabase (e.g., physical activity levels) and myACTIVEsteps.com (e.g., program engagement metrics) to cross-validate responses and reduce reliance solely on self-report.

The crossover design, while improving internal validity and allowing within-participant comparisons with fewer total participants, may introduce learning or carryover effects that complicate the interpretation of intervention-related changes. While the requirement for a co-residing or nearby care partner was included to ensure adequate exposure to intervention and safety monitoring, it may limit generalizability. In addition, dyadic-level interdependence may influence outcomes in ways that cannot be fully isolated with the pilot sample size. Finally, forgetting to wear the smartwatch every day and to charge it twice a week may introduce missing data, which may be difficult to impute depending on the pattern and volume of missingness. Despite these limitations, this pilot study lays a foundation for a scalable intervention that may improve engagement in physical activity and the quality of life of older adults and their care partners, including those with mild AD/ADRD.

The ACTIVE intervention has the potential to enhance physical activity, functional independence, and overall well-being among older adults and their care partners. At the conclusion of the ACTIVE pilot study, we plan to share the study findings with participants, care partners, and relevant stakeholders through plain-language summaries. Participants who express interest will receive a concise summary of results via email or mail. In addition, study outcomes will be posted on the ClinicalTrials.gov registry in accordance with reporting requirements. Findings will also be disseminated through peer-reviewed publications and presentations at scientific meetings to inform the broader research and clinical community.

